### 2.7. Sample Size

The calculation of the number of participants per group was based on the expected improvement in the MWD after 12 weeks in the intervention group (NMES) compared with the control group. Considering previous studies [12,14] that assessed the effects of NMES during a program of lower duration (1 month), we expected a 50% improvement in MWD in the NMES group with no significant change in the CONT group. We assumed a baseline MWD of ~115 ± 78 m in both groups. Thus, considering a between-groups difference of approximately 58 m with a standard deviation of 78 m at the end of the 12-week program, the minimum number of participants to be included in each group is approximately 29, with an alpha risk of 0.05 and a power of 80%. We anticipated that the total number of participants to be included could be 80 (40 per group), allowing for a maximum ~30% dropout rate.

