### 2.8. Data Collection, Management, and Analysis

*Data collection and management.* The data collected are in an electronic Case Report Form (eCRF) and data monitoring is carried out on a regular basis (~every six months).

*Statistical analysis (see also File S1, item 20a).* Descriptive statistics will be performed to describe the baseline characteristics of interest at the level of the two groups and for the different outcomes. Continuous data will be expressed as mean +/− standard deviation or median values with interquartile range, depending on the distribution. A normality test will be carried out to judge the Gaussian or non-Gaussian distribution of the data of the continuous variables studied. Two-sample, two-sided t-tests (or Mann–Whitney U test) and χ2 tests will be used to compare continuous and categorical characteristics of participants across the two groups at baseline, respectively.

For statistical analysis of the primary and secondary outcomes after study completion, two -sample, two-sided t-tests (or Mann–Whitney U test if the data is not normally distributed) will be used to compare changes in outcomes between baseline and the 3-month follow-up between the NMES and the CONT groups. However, in case of imbalance in baseline characteristics between the 2 groups, outcome data will be analyzed using linear regression models adjusting for significantly different baseline data between the two groups [46].

Firstly, an intention-to-treat analysis will be performed. As recommended [47], a missing at random (MAR) assumption will be made for missing data for principal analysis by performing complete cases and multiple imputation analysis. Deviation from MAR will also be assessed with sensitivity analysis under the missing not at random (MNAR) assumption, using controlled multiple imputation with different controlled scenarios. A per-protocol analysis will be also performed considering only participants with data available both at visit #1 and visit #2.

A subgroup analysis will be performed to explore the potential association between change in treadmill MWD and reported walking activity changes during the follow-up. In the NMES group, potential association between the total dose of NMES over the program and change in treadmill MWD will be assessed.

Statistical analysis will be carried out using R software [48]. The level of significance will be fixed at *p* < 0.05.

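### A normality test on the trial data chooses between t-test and Mann–Whitney for the primary outcome, so neither the test nor the effect measure is fixed, and the rank branch need not target the 58 m mean difference used for sizing

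*Protocol article*

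**What the plan says.** Section 2.8 of the protocol article announces a preliminary check: "A normality test will be carried out to judge the Gaussian or non-Gaussian distribution of the data of the continuous variables studied". For the primary and secondary outcomes, two-sided "t-tests (or Mann–Whitney U test if the data is not normally distributed" then "will be used to compare changes in outcomes between baseline and the 3-month follow-up between the NMES and the CONT groups". The rule covers maximal walking distance (MWD), the primary outcome. The article does not say which normality test applies, at what level, or on which data (each arm, pooled values or residuals). It names no effect estimate for the Mann–Whitney branch.

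The same section plans complete-case and multiple-imputation analyses under missing at random, plus controlled multiple imputation under missing not at random. It refers to File S1, item 20a, which is not shown.

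The sample size in section 2.7 rests on means. "We assumed a baseline MWD of ~115 ± 78 m in both groups"; "we expected a 50% improvement in MWD in the NMES group with no significant change in the CONT group"; and the number per group follows from "considering a between-groups difference of approximately 58 m with a standard deviation of 78 m at the end of the 12-week program".

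**The concern.** A confirmatory trial should name in advance one primary test and one effect measure. Here both depend on a significance test applied to the outcome data. This is a stated rule and not detail left to another document: a statistical analysis plan could settle it only by overriding the sentence.

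The two branches can answer different questions. The t-test compares mean changes, which is what section 2.7 plans for. Mann–Whitney compares distributions through the probability that a patient in one arm does better than a patient in the other. The two agree for a pure shift, but not in general when the arms differ in shape. A treatment that lengthens distance in proportion to baseline, or that works in only some patients, changes the shape.

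At stake are which result becomes the headline, whether it can be read against the 58 m assumption, and whether the rule defines a single analysis once missing values have been multiply imputed.

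**Working it through.** **1. The plan's own figure.** Inputs from section 2.7: difference 58 m, SD 78 m, two-sided alpha 0.05, power 80%.

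n per group = 2 × (1.960 + 0.842)² × (78/58)² = 2 × 7.85 × 1.809 = 28.4, rounded up to 29.

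The stated 29 reproduces. The exact t-test gives 29.4, hence 30. The planned quantity is a difference in means, with standardised effect 58/78 = 0.744.

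**2. How often the rule switches.** Assumptions, none of them in the article: Shapiro–Wilk at 5% in each arm, with Mann–Whitney used if either arm rejects.

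- Truly normal changes: expected 1 − 0.95² = 9.75%; simulated 9–11%.
- Lognormal MWD with mean 115 m and SD 78 m, baseline cut at 300 m, baseline-to-follow-up correlation 0.5 or 0.7, 28 per arm (40 × 0.7): 53–75%.
- Changes that are themselves lognormal (log-SD 0.5): 91% at 29 per arm, 98% at 40.

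**3. How often the choice matters.** In the lognormal-MWD scenario with a 35–50% gain, the two tests fall on opposite sides of 0.05 in about 8–13% of trials. For a pure shift of 0.744 SD, they disagree in 2–5% of trials with normal changes and in 7–19% with skewed or heavy-tailed changes.

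**4. Whether the branches estimate the same thing.**

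- *Proportional gain.* Lognormal baseline with log-variance ln(1 + (78/115)²) = 0.378; follow-up multiplied by 1.5 in the NMES arm, with a log-scale error SD of 0.3. Mean difference 0.5 × 115 = 57.5 m; Hodges–Lehmann shift 44 m.
- *30% responders.* Each responder gains 58/0.3 = 193 m, with background SD 50 m. Mean difference 58 m; shift 39 m; P(NMES better) 0.65.
- *50% responders.* Mean difference and shift are both 58 m, so divergence is possible but not inevitable.

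**5. Error rates of the two-stage rule.**

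| Scenario | Two-stage rule | t-test |
|---|---|---|
| Same distribution in both arms, null | 4–6% | 4–6% |
| Equal means, different shapes (normal, SD 50 m, against lognormal, log-SD 0.8, scaled to SD 78 m), 29 / 40 per arm | 16% / 21% | 7% / 6% |
| 50% proportional gain, correlation 0.5 (power) | 0.69–0.73 | 0.67–0.70 |
| 50% proportional gain, correlation 0.7 (power) | 0.87–0.88 | 0.84–0.86 |

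The second row is not a false-positive rate for the hypothesis that Mann–Whitney tests, because the distributions do differ. It is the rate at which the rule declares a difference when the mean difference, the quantity planned for, is zero.

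**6. Multiple imputation.** Simulated with normal changes, 29 of 40 observed per arm, 20 imputations and 1,500 trials. Pooling by Rubin's rules gave type I error 0.049 and power 0.79 for the mean difference, and 0.052 and 0.79 for the Mann–Whitney probability. The normality verdict was not the same in all 20 imputed datasets in 51% of trials under the null and 49% under the planned effect.

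**The case against.** The strongest defence is that the rule does little damage to the operating characteristics. That stands. When the arms share a distribution, type I error stays near 5%, and in the proportional-gain scenario the rule has slightly more power than the t-test. Every switching and disagreement rate above also depends on distributions, correlations and a normality test that the article does not give. File S1 or an analysis plan may add detail, and pooling mechanics are commonly left to such documents.

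A reader might infer several stronger things that the documents do not support:

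- *The rank branch cannot be pooled over imputations, or gives no effect in metres.* The Mann–Whitney probability pooled without difficulty in step 6, and a Hodges–Lehmann shift is in metres. What is true is that the article specifies neither, and gives no rule for imputed datasets that disagree on normality.
- *Skewness is near-certain.* A normal distribution with mean 115 and SD 78 puts Φ(−115/78) = 7% of distances below zero. That concerns MWD levels. The test is applied to changes, which may be negative and in which some of the skew cancels.
- *The sample size is wrong.* It reproduces.
- *A log-scale analysis should be primary because it has more power.* Such a gain would combine baseline adjustment with a model chosen to suit proportional effects, and it says nothing about the normality rule.

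The switch to regression, "in case of imbalance in baseline characteristics between the 2 groups, outcome data will be analyzed using linear regression models", is a second data-driven choice in the same paragraph. It is a separate matter and is not counted in the figures here.

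**Conclusion.** The point holds as one about prespecification and the quantity estimated. As written, section 2.8 fixes neither the primary test nor its effect measure, and one of the two branches need not target the mean difference on which section 2.7 sizes the trial. Under the stated assumptions the switch is live (roughly half to three quarters of trials with skewed distances) and changes the significance verdict between tests in about 8–13% under an effect. The gap in the quantity estimated can be material (57.5 m against 44 m), and when means are equal but shapes differ the rule rejects in 16–21% of trials against 6–7% for the t-test. Under multiple imputation the rule does not define one analysis, because the verdict can vary between imputed datasets.

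It is not a finding of general type I error inflation, lost power or an inadequate sample size.

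**What to change.** Delete the normality-test switch for the primary outcome. Prespecify one linear model for 12-week MWD (or its change) with group, baseline MWD and centre, the randomisation stratum. Report the adjusted mean difference in metres with its 95% CI, pooled over imputations by Rubin's rules. Keep Mann–Whitney, with a named effect measure, as a sensitivity analysis; a log-MWD version, giving a ratio of distances, may be added if wanted. Make the change before outcomes are examined by group.

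The cost is protocol or analysis-plan wording and one extra sensitivity analysis. No new data are needed and 29 per group is unchanged. There may be some loss of power against the rank test if changes are skewed. In the proportional-gain scenario the t-test trails the present rule by about 2–3 percentage points. For a pure shift with lognormal changes at 29 per arm, the t-test keeps about its planned 80% where Mann–Whitney would reach 92–98%. Baseline adjustment works the other way, by an amount that depends on a correlation the article does not give.

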### 2.5. Primary and Secondary Outcomes

Details are presented in File S1 (Item 2b). The primary outcome of the ELECTRO-PAD study will be the change in MWD at 12 weeks as assessed by a modified Strandness treadmill test (see outcomes assessment).

Secondary outcomes will be changes at 12 weeks in: (i) treadmill pain-free walking distance (PFWD); (ii) 6 min total walking distance; (iii) global positioning system (GPS)-measured outdoor walking capacity; (iv) ankle-brachial index (ABI); (v) daily PA level, including walking pain-manifestation assessment (see below); (vi) walking impairment questionnaire (WIQ) sub-scales and total scores; (vii) short-form health survey (SF36) score; (viii) peripheral artery questionnaire (PAQ) score; (ix) dietary questionnaire score; (x) delta from resting oxygen pressure (DROP) using TcPO_2_ during treadmill walking test and (xi) skin microvascular function assessed both at the forearm and calf levels using the laser speckle contrast imaging (LSCI) technique; and (xii) maximal walking distance according to the location of the arterial obstruction (using scan images).

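### Between-arm significance tests at baseline decide whether, and for which variables, the primary analysis is adjusted, so the primary model is set by chance imbalance and not by prognostic value

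*Protocol article*

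**What the plan says.** The endpoint is a change score (section 2.5): "The primary outcome of the ELECTRO-PAD study will be the change in MWD at 12 weeks".

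Section 2.8 then sets out a sequence:

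- **Baseline tests.** t-tests or Mann–Whitney tests, and χ2 tests, "will be used to compare continuous and categorical characteristics of participants across the two groups at baseline".
- **Default outcome analysis.** For primary and secondary outcomes alike, a two-sided t-test, or Mann–Whitney if the data are not normal, "will be used to compare changes in outcomes between baseline and the 3-month follow-up between the NMES and the CONT groups".
- **Switch.** "However, in case of imbalance in baseline characteristics between the 2 groups", the default gives way and "outcome data will be analyzed using linear regression models adjusting for significantly different baseline data between the two groups".
- **Level.** "The level of significance will be fixed at *p* < 0.05".

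The article names no covariate in advance and gives no prognostic criterion for choosing one. Centre is the stratification factor for randomisation (section 2.2), but section 2.8 gives it no place in the analysis.

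**The concern.** Allocation is randomised and concealed, so a baseline difference with p < 0.05 shows that chance produced an imbalance. It does not show that the variable predicts walking distance. Selection on that p-value has two consequences:

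- Variables unrelated to the outcome can enter the primary model.
- Baseline MWD stays out unless its own test happens to be significant, although a non-significant imbalance in it still shifts the change-score estimate.

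Which estimate, standard error and p-value count as the primary result is therefore unknown until the arms have been compared at baseline. If the adjusted and unadjusted results fall on opposite sides of 0.05, the choice is open to challenge. The trial plans for about 29 evaluable participants per arm, so it has little precision to spare.

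**Working it through.** **Inputs from the article.** Difference 58 m, SD 78 m, two-sided 0.05, power 80%, 29 per arm (section 2.7). Selection level 0.05 (section 2.8).

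**Inputs not in the article, so assumed.** The number of baseline variables tested, k (10, 15 or 20), and the correlation rho between baseline and 12-week MWD (0.3, 0.5 or 0.7).

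**1. The plan's own figure.** n per arm = 2 × (1.960 + 0.842)² × 78² / 58² = 28.4, so 29. This reproduces the stated figure by the normal approximation; the t-distribution gives 29.4, so 30. The calculation rests on the unadjusted comparison. Because SD of change = 78 × √(2(1 − rho)), using 78 m as the SD of the change amounts to rho = 0.5.

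**2. How often the model switches.** For k independent tests at 0.05 the chance of at least one significant result is 1 − 0.95^k:

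| k | Chance of switching |
|---|---|
| 1 | 5% |
| 10 | 40% |
| 15 | 54% |
| 20 | 64% |

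The first row also applies to baseline MWD on its own: it would be selected in about 5% of trials. With 15 variables and a pairwise correlation of 0.3 or 0.5 (assumed), simulation puts the chance of switching at about 46% or 36%.

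**3. What a non-significant imbalance can do.** The standard error of the baseline difference is 78 × √(2/29) = 20.5 m, so differences up to about 1.96 × 20.5 = 40 m are not selected. With equal SDs, a baseline difference D shifts the unadjusted difference in change by (1 − rho) × D, against the arm that started higher. At the 40 m limit the shift is 28, 20 or 12 m for rho = 0.3, 0.5 or 0.7, against a planned effect of 58 m. That is the extreme case; an imbalance of one standard error shifts the estimate by half as much.

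**4. Power by formula.** Power = Φ(58 / (SD × √(2/29)) − 1.96). The SD is 78 × √(2(1 − rho)) for the change score and 78 × √(1 − rho²) after adjustment for baseline MWD.

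| rho | Unadjusted | Adjusted for baseline MWD |
|---|---|---|
| 0.3 | 67% | 84% |
| 0.5 | 81% | 90% |
| 0.7 | 96% | 98% |

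**5. Power of the rule as written.** It was simulated with 29 per arm, normal data and 15 independent baseline variables of which only baseline MWD is prognostic.

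| rho | No adjustment | Plan's rule | Fixed adjustment for baseline MWD |
|---|---|---|---|
| 0.3 | 64% | 62% | 82% |
| 0.5 | 80% | 78% | 88% |
| 0.7 | 95% | 94% | 97% |

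**6. Type I error.** With no treatment effect, the rule rejects in about 0.04 to 0.05 of simulated trials.

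**The case against.** **The rule is declared in advance and uses baseline data only.** This stands. It is not outcome-driven selection, and simulated type I error is at or slightly below nominal. A reader might infer inflated false positives from a data-dependent model; the calculations do not support that.

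**The gap from 78% to 88% is not the price of the rule.** This also stands. Deleting the switch and keeping the unadjusted test would leave power at about 80% at rho = 0.5. The rule itself costs about 0 to 2.5 points. Most of the gap comes from having no fixed adjustment for baseline MWD.

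**Baseline is not ignored.** The change score subtracts it, and when its imbalance is significant the rule does adjust. In those trials, null rejection is about 13% to 18% unadjusted and about 5% after adjustment. But that covers only about one trial in twenty. The article does not say that baseline MWD is the strongest predictor; the point needs only that a change score is tied to its baseline.

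**The assumptions can be softened.** Baseline walking measures are plausibly correlated, which lowers the chance of switching. If all 40 per arm are evaluable and rho = 0.5, power is about 91% unadjusted, 91% under the rule and 97% with fixed adjustment. The cost shrinks but the ordering between the rule and fixed adjustment remains.

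**Is the non-normal and imbalanced case undefined?** A reader might infer so. The text does not support it: the imbalance clause comes after both default tests and overrides them, so linear regression applies whatever the distribution.

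**File S1, item 20a, is not shown.** It may add covariates or detail. The point concerns a rule that the article states outright, and that rule needs correcting either way.

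**Conclusion.** The point holds. As printed, chance imbalance decides both whether the primary analysis is adjusted and for what. With 10 to 20 independent baseline variables the model would switch in 40% to 64% of trials, while baseline MWD would be a covariate in only about 5%.

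The harm is a primary model and estimate not fixed in advance, and lost precision. Against fixed adjustment for baseline MWD, the rule gives up about 20 points of power at rho = 0.3 (82 − 62), 10 at rho = 0.5 (88 − 78) and 3 at rho = 0.7 (97 − 94). Only 0 to 2.5 of those points are due to the significance-based selection.

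These figures rest on assumed values of k and rho, normal data and 29 evaluable per arm. That the model depends on chance follows from the text alone. Severity: should-fix.

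**What to change.** - Delete the between-arm significance tests as a means of choosing covariates, and present baseline characteristics descriptively.
- Make the primary analysis one linear model (ANCOVA) of 12-week MWD change on treatment, adjusted for baseline MWD and centre, fitted whatever the baseline comparison shows.
- Keep the unadjusted comparison, and any model that adds variables seen to be imbalanced, as labelled sensitivity analyses.
- Settle this before outcomes are compared by arm.

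The cost is wording in the protocol and analysis plan. It needs no extra participants, visits or data, since baseline MWD and centre are already recorded.

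### Complete-case analysis and multiple imputation are both placed under MAR without saying which is primary, but the unadjusted completer test of change is not MAR-valid in general

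*Protocol article*

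**What the plan says.** Section 2.5 fixes the endpoint: "The primary outcome of the ELECTRO-PAD study will be the change in MWD at 12 weeks". Section 2.8 says that two-sample t-tests, or Mann–Whitney tests if the data are not normal, "will be used to compare changes in outcomes between baseline and the 3-month follow-up between the NMES and the CONT groups". Covariates enter only if the groups turn out to be imbalanced at baseline, in which case "outcome data will be analyzed using linear regression models adjusting for significantly different baseline data between the two groups".

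On missing data, the same section says that "a missing at random (MAR) assumption will be made for missing data for principal analysis by performing complete cases and multiple imputation analysis". It does not rank the two analyses. Departures from MAR are to be examined "using controlled multiple imputation with different controlled scenarios". The per-protocol analysis is defined as "considering only participants with data available both at visit #1 and visit #2", which for change in MWD is the complete-case set.

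Section 2.7 sets 40 per group, "allowing for a maximum ~30% dropout rate".

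**The concern.** One sentence gives two analyses the same assumption, although they rest on different ones. Under MAR, dropout may depend on observed data such as baseline MWD. Change from baseline also depends on baseline, because of regression to the mean. If baseline-related dropout differs by arm, the completers' baselines no longer match, and the unadjusted difference in change shifts although MAR holds.

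Nothing else in Section 2.8 repairs the completer test:

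- The conditional adjustment responds to imbalance at baseline, not to selective loss afterwards.
- The MNAR scenarios address departures from MAR, whereas this bias arises within it.
- The per-protocol set repeats the complete cases, so its agreement with the complete-case result would be no corroboration.

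Dropout that differs by arm is possible here. Participants learn their allocation, and only the NMES group is asked for 2 to 3 hours of stimulation a day, five days a week, for 12 weeks. At stake is a complete-case result reported as MAR-valid that could be wrong in either direction.

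**Working it through.** **The plan's own figure.** Section 2.7 is "considering a between-groups difference of approximately 58 m with a standard deviation of 78 m at the end of the 12-week program", with alpha 0.05 and 80% power. n per group = 2 × (1.96 + 0.842)² × 78² / 58² = 28.4, so 29. This reproduces. Forty per group leaves 29 at 1 − 29/40 = 27.5% loss, in line with a maximum of roughly 30%.

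**Inputs from the document.** Baseline MWD 115 m, SD 78 m; expected gain 50%, which is 0.5 × 115 = 57.5 m; dropout 30%.

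**Assumptions not in the document.** Baseline and 12-week MWD are bivariate normal, both with SD 78 m, with correlation ρ from 0.3 to 0.9. Dropout is 30% in each arm and depends only on baseline MWD (so MAR holds), through a logistic model with log-odds changing by 0.5 or 1.0 per baseline SD.

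**Constant effect.** Within an arm, expected change at baseline z-score z is the arm's mean change minus (1 − ρ) × 78 × z. If completers have mean z-scores m_N (NMES) and m_C (control):

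completer difference = 57.5 − (1 − ρ) × 78 × (m_N − m_C)

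When poorer walkers leave, numerical integration gives m = 0.143 (log-odds 0.5) or 0.253 (log-odds 1.0). When better walkers leave, the sign reverses. If dropout is unrelated to baseline, m = 0.

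Example at ρ = 0.5, log-odds 1.0, NMES only: 57.5 − 0.5 × 78 × 0.253 = 47.6 m.

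| ρ | Poorer leave NMES only, 0.5 | Same, 1.0 | Better also leave control, 0.5 | Same, 1.0 |
|---|---|---|---|---|
| 0.3 | 49.7 | 43.7 | 41.9 | 29.9 |
| 0.5 | 51.9 | 47.6 | 46.4 | 37.8 |
| 0.7 | 54.2 | 51.6 | 50.8 | 45.7 |
| 0.9 | 56.4 | 55.5 | 55.3 | 53.6 |

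Entries are metres against a true 57.5 m. Reversing the patterns gives the same errors upward. With equal patterns and rates, m_N = m_C and the bias is zero. Simulation with 2,000,000 per arm agrees for the log-odds 1.0 patterns run.

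**Type I error.** Simulated with 40 per arm, a nominal 5% test, log-odds 1.0 and ρ of 0.5 and 0.7: about 6 to 7% for one-arm dependence, 11 to 16% for opposite patterns, and 4.7% for the same pattern in both arms.

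**Effect proportional to baseline.** This is one reading of the 50% improvement. The NMES effect becomes 57.5 + 39z, so 39 × m_N is added to the formula. At log-odds 1.0:

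- Same pattern in both arms, poorer walkers leaving: 57.5 + 39 × 0.253 = 67.4 m at every ρ, an error of about 10 m.
- Poorer walkers leave NMES only, ρ = 0.5: the two terms cancel (39 × 0.253 − 39 × 0.253) and the unadjusted test gives 57.5 m.

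**Does a common-slope baseline term rescue the completers?** With a constant effect, yes. With a proportional effect, not always. In the NMES-only case at ρ = 0.5, the slope of change on z is 0 in NMES and −0.5 × 78 in control. Weighted by the completers' baseline variances in z units (0.860 and 1), the pooled slope is −0.5/1.860 × 78 = −0.269 × 78. The adjusted estimate is 57.5 + 0.269 × 78 × 0.253 = 62.8 m. With the same pattern in both arms it stays at 67.4 m. With opposite patterns it is correct (57.5 m, against 47.6 m unadjusted at ρ = 0.5). At log-odds 0.5 in NMES only, the error is about 3 m.

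**Imputation by arm from baseline MWD** gave a bias of about 0 m in every simulated pattern, including the proportional effect.

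**The case against.** The strongest reply is that the quoted sentence also plans multiple imputation, a standard MAR method, and that Section 2.8 adds MNAR scenarios. This stands. A reader might infer that the trial's primary estimate is biased; the document does not support that, because nowhere does it make the complete-case result the sole or leading one.

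A reader might also infer that the completer test needs dropout to depend on nothing but arm. That is sufficient, not necessary. Dropout may depend on factors unrelated to change, or on baseline equally in both arms if the effect is constant, without bias.

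The sizes rest on assumed correlations and dropout slopes, 30% is a stated maximum, and the largest errors need opposite selection in the two arms. Control participants also receive fortnightly calls meant to aid retention, on the same schedule as the NMES group. These points limit the likely size but do not make the MAR label right.

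Finally, the details of the imputation model, and perhaps the ranking, may sit in File S1 item 20a or an analysis plan, neither of which is shown. Leaving such detail out is no fault. The point here is what the article states: it puts an unadjusted completer comparison under an assumption that does not support it.

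**Conclusion.** The concern holds in a limited form. Section 2.8 describes complete-case analysis as resting on MAR, and for the stated unadjusted test of change that is wrong in general. With a constant effect of 57.5 m, 30% dropout and ρ of 0.3 to 0.7, the completer difference would be about 44 to 54 m under one-arm selection (log-odds 0.5 to 1.0). Under opposite selection it would be about 30 to 46 m at log-odds 1.0, or 42 to 51 m at 0.5. At ρ = 0.9 the error is about 1 to 4 m. It is zero with equal patterns and a constant effect, and it can go either way. These are illustrations under a normal model, not forecasts.

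The primary estimate is exposed only if the complete-case result becomes primary. The text permits that, because it does not rank the two analyses. Nor should one conclude that a baseline term alone makes the complete-case analysis MAR-valid: if the effect is proportional to baseline, a common-slope term leaves about 3 to 10 m of bias in several patterns.

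**What to change.** In Section 2.8 and the analysis plan:

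- Name one primary analysis: multiple imputation done separately by arm, with baseline MWD and centre in the imputation model, analysed by a model pre-specified to adjust for baseline MWD and centre whether or not the groups differ at baseline.
- Keep the unadjusted completer test only as a supportive analysis, and state its stricter assumption: within each arm, missingness is unrelated to predictors of change.
- Do not describe a complete-case regression with a common baseline slope as MAR-valid without the further condition that the effect does not vary with baseline.
- Keep the MNAR scenarios as departures from the named primary analysis.

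The cost is a change of wording and slightly more analysis. No new data are needed, since baseline MWD and centre are already recorded.
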